## Abstract

**Background:**

Depression and anxiety are common and co-morbid disorders that affect a significant proportion of students. Innovative prevention strategies targeting both conditions are needed to reduce their health burden and costs. ICare Prevent is such an innovative strategy and contains a transdiagnostic individually tailored Internet-based and mobile-supported intervention. It addresses common risk factors of depression and anxiety as part of a large EU-funded multi-country project* (ICare). Little is known about the clinical and cost-effectiveness of this type of intervention compared to care as usual (CAU) for college students. We hypothesize that ICare Prevent will be more (cost-)effective than CAU in the reduction of symptoms of depression and anxiety.

**Methods:**

A three-arm, parallel, randomized controlled superiority trial will be conducted comparing a guided and an unguided version of ICare Prevent with a control group receiving CAU. The trial will be open-label but outcome assessors will be blinded. A total of 252 college students (age ≥ 16 years) with subclinical symptoms of depression defined as a score ≥ 16 on the Center for Epidemiological Studies Depression Scale (CES-D), and/or anxiety, defined as a score ≥ 5 on the Generalized Anxiety Disorder scale (GAD-7), will be included. Those meeting diagnostic criteria for a depressive or anxiety disorder will be excluded. The primary outcome is change in disorder specific symptom severity from baseline to post-intervention. Secondary endpoints include self-reported depression and anxiety symptoms as well as time to onset of a mood or anxiety disorder until 12-month follow-up. Societal costs and quality of life will be assessed to estimate the intervention’s cost-effectiveness compared to CAU.

**Discussion:**

Transdiagnostic individually tailored Internet-based prevention could be a (cost-)effective approach to tackle the disease burden of depression and anxiety among college students.

**Trial registration:**

Dutch trial register, NTR 6562. Registered on 6 July 2017.

**Electronic supplementary material:**

The online version of this article (10.1186/s13063-018-2477-y) contains supplementary material, which is available to authorized users.

## Background

Depression and anxiety are highly prevalent and debilitating conditions that are associated with considerable economic costs [1–5]. Both disorders have their peak onset in early adulthood, including college years [6, 7]. College students often experience a variety of stressors (e.g. gaining personal and financial independence), which have the potential to trigger or exacerbate symptoms of mental health conditions [8, 9]. Correspondingly, > 20% of all college students suffer from a mental condition, ranking anxiety and depression on top [10–12].

Depression and anxiety during college years have several negative consequences for students and society. For example, a younger age of onset of depression and anxiety has been linked to a more severe and chronic disease trajectory, as well as a higher risk for developing co-morbid psychiatric disorders in adulthood [8, 13, 14]. Moreover, it is clear that anxiety and depression negatively influence academic performance and increase the possibility of college dropout [15, 16]. On a societal level, college students’ untreated depression and anxiety may have significant implications for human capital, specifically when their future employment and income is considered [17, 18].

Preventing the development of these mental health conditions in college students is thus of great importance. Hence, recommendations have been made to implement university-based early detection and prevention programs [19]. These can be distinguished as universal (targeting a population as a whole), selective (providing an intervention to individuals with a specific risk profile), and indicated (targeted to those who already experience elevated symptoms below clinical thresholds) ([20]; p. 20–21). According to previous research, face-to-face college-based universal prevention programs show small to moderate effects in reducing depression or anxiety severity [21]. Yet, data on selective and indicated university-based prevention approaches are scarce, though their application may be particularly effective because they are targeted at those who need help the most ([22], p. 499). Specifically, indicated prevention has been described as the preferred approach based on its potential for detecting and efficiently helping those who have a high risk of developing depression [23].

Internet-based interventions have the potential to fill the gap between the limited university healthcare facilities and the treatment demand [24–26]. In contrast to face-to-face psychotherapy, this approach depends less on therapist availability, offers low-threshold access, and the possibility to use the intervention at any time and place. Moreover, it provides a high degree of anonymity and thus tackles the issue of stigma associated with mental health problems, which negatively affects college students’ help-seeking behavior [17, 18]. In clinical populations, the effectiveness of such Internet-based interventions for anxiety and depression has already been established [27, 28], especially if they are provided with some form of therapeutic guidance [29]. With regard to prevention of depression or anxiety, the evidence regarding the effectiveness of Internet-based interventions is inconclusive. Recent trials comparing indicated prevention programs to controls have shown mixed effects, varying from no differences between the conditions to moderate effects on reduction of incidence rates in favor of the Internet-based preventive program [24–26, 30, 31].

However, to the best of our knowledge, no randomized controlled trial on the effects of online indicated prevention of depression and anxiety has been conducted in a pure college student population. Moreover, past research has largely focused on disorder-specific interventions for the online treatment and prevention of these conditions. Adding transdiagnostic components may address their co-morbidity better, as well as common underlying factors, such as general negative affect and disturbed information processing [32]. Recent meta-analytic evidence on Internet-based interventions has shown that transdiagnostic approaches have no differential effect for anxiety when compared to disorder specific approaches, but they do perform significantly better in the reduction of depressive symptoms [33].

Finally, the cost-effectiveness of Internet-based indicated prevention programs and the added value of human support remain unclear. Though some studies suggest that Internet-based treatment has the potential to be cost-effective [24–26, 34–36], the evidence for prevention is limited. The economic evaluation of the Internet-based prevention program developed by Buntrock et al. [37] shows that such an indicated prevention of depression through the Internet can have a large likelihood to be cost-effective when compared to enhanced usual care. Moreover, although asynchronous support (e.g. by email) has been shown to have beneficial effects on outcomes and retention [38–40], information on the cost-effectiveness of such an investment (e.g. time and costs of eCoach) as compared to no human support for Internet-based prevention of anxiety and depression among students is lacking. Examining further the cost effectiveness of guided and unguided Internet-based indicated prevention in a student population is essential.

## Methods/Design

The study is a three-arm, parallel, randomized controlled superiority trial, with an economic evaluation alongside, for college students with subclinical symptoms of depression and/or anxiety. An unguided and a guided version of ICare Prevent will be compared to CAU in a Dutch university setting. Next to screening for eligibility, self-report measures and clinical interviews will be administered at baseline, mid-intervention, and post intervention, as well as at six-month and 12-month follow-ups. The ethics committee of the VU medical center has approved the study (number NL60705.029.17). A populated SPIRIT checklist and figure have been submitted as additional files to this publication (see Additional file 1 for SPIRIT checklist and SPIRIT figure (Additional file 2).

### Participants

Students will be recruited and provided with contact details through e.g. a website (https://icare-online.eu/nl/), social media (e.g. Facebook), and information material distributed on campus at Dutch universities. They are eligible if they: (1) are aged ≥ 16 years; (2) experience at least mild self-reported symptoms of depression, defined as a score ≥ 16 on the Center for Epidemiological Studies Depression scale (CES-D; [41]), and/or anxiety, defined as a score ≥ 5 on the seven-item version of the Generalized Anxiety Disorder scale (GAD-7; [42]); (3) do not meet diagnostic criteria for a mood or anxiety disorder based on the Mini International Neuropsychiatric Interview (M.I.N.I.; [43]) at screening. Exclusion criteria are: (1) being on a waitlist for, currently receiving, or having received psychotherapy over the past six months for any mental health condition; (2) meeting diagnostic criteria for a lifetime bipolar disorder (M.I.N.I.) or having received a diagnosis of a psychiatric disorder; (3) being at moderate to severe risk for suicide (M.I.N.I.); (4) being in remission of a major depressive disorder (MDD) episode, defined as an MDD diagnosis in the previous six months and experiencing at least one cardinal symptom (e.g. persistent and pervasive low mood, loss of interest or pleasure in usual activities) during the previous three weeks (M.I.N.I.); (5) self-reported inability to read or write Dutch; (6) no informed consent; (7) no access to a computer or the Internet; or (8) participating in similar studies at time of inclusion.

### Study procedures

Upon contact, potential participants will receive an information letter and informed consent form by email, the latter to be signed and returned. In addition, the email contains a link to the ICare Prevent platform on which participants have to register. After the informed consent form has been returned, the screening questionnaires for all self-reported inclusion and exclusion criteria will be made available on the platform. The screening consists of: demographic questions; the CES-D; and the GAD-7. Next, eligible participants will be asked for their telephone number in order to conduct the M.I.N.I. interview, the clinician rated version of the Quick Inventory for Depression Scale (QIDS-CR; [44]) and the Structured Interview Guide for the Hamilton Anxiety Rating Scale (SIGH-A; [45]). The interviews will be performed by trained clinical psychology master students under the supervision of a member of the research team; 10% will be recorded and rated by a second rater to assess inter-rater reliability. Consent for the recordings will be asked for at the beginning of the call. Disagreement between raters will be solved by discussion or by asking an experienced psychotherapist. Eligible participants will receive a confirmation by email and access to the baseline self-report questionnaires on the online platform. Once completed, they will be randomized to one of the two intervention conditions or the control group.

Non-eligible participants will be advised to consult their general practitioner or a (student) psychologist if they think they need help for their complaints. Those with moderate to severe suicide risk will also be advised to contact their general practitioner. In addition, they will be informed about the national suicide helpline (113online; [46]). The research team will contact those participants again one week later and ask whether they sought help.

### Randomization, treatment allocation, and blinding

The allocation scheme will be derived by computer using a random number generator at a 1:1:1 ratio. Participants will be randomized at an individual level by an independent institute (University of Münster, Germany) and randomization will be stratified by type of subclinical symptoms (depression or anxiety). Due to the nature of the study it is not possible to blind either participants or coaches, as they will be notified to which of the three conditions they have been assigned to. However, raters who perform the clinical interviews to assess outcomes will be blinded. In order to ensure that blinding was successful, participants will be informed about the importance not to indicate their allocation status at the beginning of the telephone interviews. Moreover, raters will be asked to guess the allocation status of each participant after the second interview at post intervention. The results will then be compared to what would have been expected by chance. The flowchart of the trial is shown in Fig. 1.

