### Intervention

ICare Prevent is an Internet-based intervention with mobile-support by means of an application (app). It uses both transdiagnostic and individually tailored components that are based on previously developed Internet-based modules, all using evidence-based CBT principles [47–51]. ICare Prevent consists of seven main sessions and one booster session. Participants are advised to complete one main session per week. The intervention contains text, exercises, images, explanatory videos, as well as audio files and downloadable information. Testimonials are used to illustrate (homework) exercises. The main sessions follow the same basic structure. First, the content of the current session is explained, followed by a review of the homework exercises from the previous session. In accordance with the individually tailored approach of the intervention, participants can choose content depending on their predominant complaints, i.e. depression or anxiety. For example, in the fifth session, participants can either practice problem-solving or exposure techniques. The content per session is summarized in Table 1. Throughout sessions 2–7, participants can choose to complete one of eight choice modules following the main intervention content. In accordance with the transdiagnostic approach of the intervention, these modules aim at increasing resilience and tackle problems common to both depression and anxiety. In addition, five diaries with different content, such as positive activities and sleep, are accessible through the online platform and the app. An overview of all choice modules and diaries is given in Table 2.

**Table 1 Tab1:** Overview of topics covered by the intervention per session

Session	Topic
1	Introduction, technical aspects, goal-setting, and behavioral activation in the context of basic psychological needs and important personal values
2	Identifying problems and tackling them through behavioral activation
3	Psychoeducation on depression and anxiety
4	Cognitive restructuring and challenging negative thoughts
5	Identifying the most prominent complaints and accordingly follow either:
	a) problem-solving strategies for more prominent depressive complaintsb) exposure strategies for more prominent anxiety complaints
6	Deepening the training on the route chosen in session 5
7	Making a plan for the future
8	Booster session (four weeks after session 7)

**Table 2 Tab2:** Overview of topics covered by the choice modules and diaries

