### Statistical analysis

All analyses for the primary and secondary outcomes will be based on multilevel mixed model regression analyses for continuous outcomes in order to assess change over time. Time will be used as a predictor variable and baseline measures will be included as covariates. Linear models will be used for normally distributed data and negative binomial models for left-skewed data. All analyses will be performed on an intention-to-treat (ITT) sample. Per-protocol analyses including only participants who conformed to their group allocation will be performed in addition. Missing data will be handled using either multiple regression imputation techniques if appropriate or full information maximum likelihood estimation [106]. The secondary outcome, time to mental health disorder onset during 12 months follow-up in all conditions, measured by the M.I.N.I., will also be compared using survival curve analysis. The curves will be compared using cox proportional hazard regression analysis using baseline symptom severity as a covariate. Hazard ratios will be calculated as measure of the effect size of group differences. Within secondary analyses, interactions with predictors will be added to the model in order to identify risk and protective factors.

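### Students who meet both symptom cut-offs have no stated randomization stratum, and the models described do not name the stratification factor

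*Protocol article*

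**What the plan says.** Under Participants, a student qualifies who must "experience at least mild self-reported symptoms of depression, defined as a score ≥ 16 on the Center for Epidemiological Studies Depression scale" "and/or anxiety, defined as a score ≥ 5 on the seven-item version of the Generalized Anxiety Disorder scale". The conjunction makes three groups eligible: CES-D at or above 16 only, GAD-7 at or above 5 only, and both.

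Under Randomization, treatment allocation, and blinding, allocation is 1:1:1 by an independent institute, and "randomization will be stratified by type of subclinical symptoms (depression or anxiety"). Two levels are named.

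Under Statistical analysis, the mixed models are described thus: "Time will be used as a predictor variable and baseline measures will be included as covariates". Time to onset is to be analysed by "cox proportional hazard regression analysis using baseline symptom severity as a covariate". The stratification factor is named in neither place, and neither place rules it out.

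Two other statements bear on the point. The abstract's Background opens with "Depression and anxiety are common and co-morbid disorders that affect a significant proportion of students". The Intervention section says that "participants can choose content depending on their predominant complaints, i.e. depression or anxiety".

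**The concern.** The strata do not map onto the eligibility rule. A student above both cut-offs fits either named level or neither, and the article does not say which. Both cut-offs mark mild symptoms and the transdiagnostic rationale rests on co-morbidity, so this group is unlikely to be rare, although the documents give no share for it.

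The primary outcome is disorder-specific severity on two instruments (QIDS-CR and SIGH-A), so symptom type is plausibly prognostic. Two things are then at stake. First, if co-morbid students are distributed over two strata, stratification does not by itself balance the arms within that subgroup, and a reader cannot reconstruct the strata. Second, if allocation is balanced on a prognostic factor and the model omits it, the standard error does not reflect the balance gained: tests become slightly conservative and some power is lost.

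**Working it through.** **1. Do the passages agree?**

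| Screening result | Eligible (Participants) | Named stratum (Randomization) |
|---|---|---|
| CES-D ≥ 16 only | yes | depression |
| GAD-7 ≥ 5 only | yes | anxiety |
| both | yes | none stated |

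The nearest thing to a rule is the reference to predominant complaints under Intervention. That is a choice of content made by the participant during the programme, after randomization and only in the two intervention arms. It cannot define a stratum for all three arms.

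The share meeting both is unknown. At an assumed 40% to 70%, it would be 0.4 × 252 = 101 to 0.7 × 252 = 176 students. The mismatch does not depend on that figure.

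**2. Does the sample size depend on this?** No. The stated 252 reproduces as a three-group one-way F test at α = 0.05 with 0.25 taken as Cohen's f: λ = 252 × 0.25² = 15.75, power 0.951. Stratification does not enter. How the article labels the 0.25 is a separate matter.

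**3. What does omitting the stratum cost?** All inputs other than N are assumptions:
- N = 252, 84 per arm, blocks of 6 within three strata with shares of 15%, 25% and 60% (the last being both);
- baseline coefficient 0.5, residual SD 0.866 (variance 0.75), and a baseline mean 0.5 SD higher in the co-morbid group;
- an effect g of the co-morbid stratum on outcome that remains after baseline adjustment: 0, 0.3 or 0.6 SD;
- analysis by ANCOVA on baseline at one time point, 4,000 runs per setting.

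| g | Type I error, omitted | Type I error, included | Power at 0.35 SD, omitted | Power at 0.35 SD, included |
|---|---|---|---|---|
| 0 | 0.057 | 0.056 | 0.743 | 0.740 |
| 0.3 | 0.044 | 0.046 | 0.733 | 0.740 |
| 0.6 | 0.041 | 0.051 | 0.712 | 0.744 |

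Simulation error is about √(0.05 × 0.95 / 4000) = 0.003 for type I error and √(0.74 × 0.26 / 4000) = 0.007 for power.

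**4. Check by formula.** Variance of the co-morbid indicator: 0.6 × 0.4 = 0.24. Its covariance with baseline: 0.5 × 0.24 = 0.12. Baseline variance: 1 + 0.25 × 0.24 = 1.06. Indicator variance not explained by baseline: 0.24 − 0.12²/1.06 = 0.226. The stratum therefore adds v = 0.226 g² to the residual variance, and the interval widens by 1/√(1 − R²) with R² = v/(0.75 + v):
- g = 0.3: v = 0.020, R² = 0.026, ratio 1.014;
- g = 0.6: v = 0.082, R² = 0.098, ratio 1.053.

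The arm effect of 0.35 divided by its standard error √(0.75 × 2/84) is 2.619.
- Stratum included: power = Φ(2.619 − 1.96) = 0.745.
- Stratum omitted, g = 0.6: power = Φ(2.619 − 1.96 × 1.053) = 0.711; type I error = 2 × [1 − Φ(2.064)] = 0.039.

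These agree with the simulation.

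**5. If co-morbid students are split over two strata.** The simulation treats them as a stratum of their own. If allocation does not separate them, the estimate itself is more variable and the test stays near its nominal level. Power without any term for co-morbidity at g = 0.6 is then Φ(2.619/1.053 − 1.96) = 0.70, against 0.745 with a three-level covariate. This is about 4 points, and the three-level term recovers it.

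**The case against.** The article condenses a fuller protocol. Its Statistical analysis section does not even name treatment arm as a model term, so it is not a full specification, and a complete covariate list commonly sits in an analysis plan that is not shown. That stands: the missing stratum is not an error, and the model term is offered as a recommendation.

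The independent institute may also hold a written rule, such as assignment by predominant symptom or a separate level for both. A reader might infer that co-morbid students have no stratum or are placed arbitrarily. The documents do not support that; they show only that no rule is stated. What remains is that the article does fix the factor and its levels, and these do not match its own eligibility rule.

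A reader might also infer that balance is lost for these students, or that the comparison is biased. Neither follows. They are randomized 1:1:1 like everyone else, and any rule based on screening scores balances them together with the others in their stratum.

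Nor can the point be enlarged by calling the trial short of power. The article states power of 0.95, and its limitations concede too little only for guided versus unguided, disorder onset, and moderators and mediators.

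Finally, recruitment began in July 2017 and the data are to be pooled with sister trials of similar design. Restratifying midway would create two schemes in one trial, so it is not proposed.

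**Conclusion.** The point holds as a free improvement. Eligibility and stratification need to be reconciled for students who meet both cut-offs, and the factor should be named in the models. That part rests on the text alone.

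The size rests on assumed values and is small: 0 to about 3 points of power and a test that is at most slightly conservative, or about 4 points with no conservatism if the strata split the co-morbid group. The upper figures need a 0.6 SD difference that remains after baseline adjustment. If baseline scores already carry that information, the loss is near zero. The calculation covers one post-intervention time point; the planned repeated-measures model may differ somewhat. No bias arises, and the sample size is unaffected.

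**What to change.** 1. State in Randomization, treatment allocation, and blinding to which stratum a student meeting both cut-offs is assigned, using the CES-D and GAD-7 scores from screening (T0). If the institute already applies a rule, report that rule.
2. Include the stratum actually used at randomization as a fixed effect in the primary and secondary mixed models, and as a stratum in the Cox model.
3. If that stratum does not separate co-morbid students, use as a baseline covariate the three-level factor (CES-D only, GAD-7 only, both) derived from T0 scores. Should the rule place all of them in one of the two strata, the three-level factor already contains the two-level one and can replace it as the fixed effect.
4. Leave the allocation list as it is.

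The cost is one sentence and one or two model terms. Both scores are recorded before randomization, so no new data are needed, and the terms should be fixed before unblinded data are examined.
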